#### Statistical methods

Regarding the primary objective, we will compare the evolution of BMI between baseline and after 12 month follow-up in the MFT and SFT groups, using an analysis of covariance (ANCOVA) with BMI at inclusion as a pre-specified co-variable, as well as inpatient status versus outpatient care.

As recommended by the Consolidated Standards of Reporting Trials (CONSORT) guidelines for non-inferiority clinical trials [87], the confidence interval of the intergroup difference of the principal criterion thus obtained will be calculated and represented graphically. The decision to conclude in favor of the non-inferiority of MFT in comparison with SFT will be made only if the upper boundary of the confidence interval is below the chosen non-inferiority threshold of 0.75 kg/m^2^.

It is recommended to carry out a double approach, intention to treat (ITT) and per protocol (PP), for the analysis of the principal criterion in cases of non-inferiority clinical trials [88], as the non-observation of a randomized treatment could reduce differences in efficacy of the two treatments and could therefore bias the trial results. The ITT analysis will include all patients randomized in their randomization group, whatever the treatment they have actually received. The PP analysis will only include patients who have followed at least three sessions without any treatment change or protocol violation. Then, in a sensitivity analysis, we will add age and illness duration to the models as co-variables, as they are important prognostic factors. Finally, if non-inferiority has been demonstrated, the superiority of the MFT treatment over the SFT treatment will be assessed in ITT.

Regarding the secondary outcomes, financial cost and satisfaction will be analyzed for the superiority of the MFT treatment over the SFT treatment. We will compare subject and parent satisfaction with the treatments (as evaluated by the CSQ-8 and ECI) at 12 months using an ANCOVA, with the status of treatment is a co-variable at inclusion (outpatient or inpatient) as a pre-specified co-variable.

In order to compare financial costs between SFT and MFT, we will make an inventory of the treatments, and we will use the average cost for each ambulatory appointment (psychiatrist, psychologist, etc.) and the average treatment cost for hospitalization if necessary during follow-up; the sum will determine the total cost of treatment for each patient. Transport costs and other associated costs will not be estimated, as most patients live near the hospital. Costs for the two treatment groups will be compared using Fisher-Pitman’s test.

An analysis of quantitative variables (assessment scores) will be performed in the same way as for the principal criterion using an ANCOVA, with the value of each respective variable at admission, and for the status of treatment at inclusion (ambulatory care or hospitalization), as co-variables. Morgan- Russell GOAS scores (with the three following outcomes: good, intermediate, and poor) will be compared between SFT and MFT, using Cochran-Armitage’s tendency test. A measure of ordinal association (Somers’ *D*) will be calculated with a confidence interval of 95%. Amenorrhea and other qualitative variables will be compared using Fisher’s exact test. Additionally, for the clinical variables assessing outcome, analyses looking for moderators and treatment effect mediators will be carried out.

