### Participants

#### Inclusion criteria

All patients treated in outpatient care or hospitalized for AN in one of the three study sites (Pr. [name]’ unit at Institut Mutualiste Montsouris, Paris; Pr. [name]’s unit at the Maison des Adolescents, Cochin Hospital, Paris; Pr. [name]’s unit in Rouen University Hospital) will be offered participation in the study if they (1) have a Diagnostic and Statistical Manual of Mental Disorders fifth edition (DSM-5) diagnosis of AN or a diagnosis of Eating Disorder Not Otherwise Specified (EDNOS), (2) are aged between 13 to 19 years, (3) have been diagnosed with AN or EDNOS before 19 years old, (4) benefit from a social welfare program, (5) live, and their family lives, in Paris and its suburbs or Rouen or in the vicinity of Rouen.

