#### Randomization

All patients who give consent for participation and who fulfill the inclusion criteria will be randomized. Randomization will be centralized and stratified according to the status of treatment at inclusion (outpatient care or hospitalization) and the center. A randomization list will be generated by computer, with blocks of variable sizes, by a statistician independent from the group recruiting or taking care of the patients. The allocation ratio will be 1:1. Results of the randomization will be accessible on the comprehensive software used for the trial (CleanWeb™). Family therapy (MFT or SFT) will start during the month following the randomization.

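### Randomisation is stratified by centre, but no planned analysis model includes centre, so the primary interval may be wider than it needs to be

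*Protocol article*

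**What the plan says.** All places are in the protocol article.

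- **Randomization:** "Randomization will be centralized and stratified according to the status of treatment at inclusion (outpatient care or hospitalization) and the center", and "The allocation ratio will be 1:1". Inclusion criteria recruits from "one of the three study sites".
- **Statistical methods, primary outcome:** an ANCOVA of BMI change to 12 months, with BMI at inclusion "as a pre-specified co-variable, as well as inpatient status versus outpatient care". Centre is not listed.
- **Statistical methods, sensitivity analysis:** "we will add age and illness duration to the models as co-variables, as they are important prognostic factors".
- **Statistical methods, satisfaction:** an ANCOVA with treatment status at inclusion. Centre is not listed.
- **Statistical methods, other scores:** an ANCOVA with the baseline value and treatment status. Centre is not listed.
- **Statistical methods, costs:** "Costs for the two treatment groups will be compared using" the Fisher-Pitman test, with no stratum named.
- **Statistical methods, categorical outcomes:** GOAS category is compared by the Cochran-Armitage test. "Amenorrhea and other qualitative variables will be compared using" Fisher's exact test. No stratum is named for either.

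**The concern.** Stratified randomisation balances the arms on the stratification factors, which lowers the true variance of the treatment difference if those factors are prognostic. A model that omits such a factor leaves its variation in the residual, so the reported standard error is larger than the true one and the benefit of stratifying is partly lost. Here status is carried through and centre is not.

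This is more than detail awaiting an analysis plan, because the article lists the covariates and calls them pre-specified.

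The primary conclusion rests on whether one confidence bound clears 0.75 kg/m², in a trial planned at 80% power. Interval width therefore bears directly on the chance of a conclusive result. The article itself describes age and illness duration as important for prognosis, yet the deciding interval makes no use of them.

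**Working it through.** **Inputs from Sample size:** margin 0.75 kg/m², SD of BMI change 1.45, one-sided 2.5%, power 80%, dropout 20%. The true difference is taken as 0, which the article does not state.

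**1. The plan's own figure.**
- Normal approximation: n = 2 × (1.96 + 0.8416)² × 1.45² / 0.75² = 58.7, so 59 per group.
- Exact noncentral t: power is 79.6% at 59 and 80.2% at 60, so 60 per group.
- Dropout: 60 / (1 − 0.20) = 75 per group.

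The stated 60 and 75 reproduce. They use the SD of raw change and take no credit for covariates.

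**2. Adding centre, age and illness duration together.** Three sites cost 2 degrees of freedom, and the two continuous covariates cost 2 more. The documents give no variance share, so the extra R² is an assumption. The SD of 1.45 is treated as the residual SD before these covariates enter, although baseline BMI and status in the planned model may already lower it.

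Residual SD = 1.45 × √(1 − R²), and SE = residual SD × √(2/60). At R² = 0, SE = 0.265. The 95% half-width is 1.981 × SE (114 df). Power is from the noncentral t.

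| Extra R² (assumed) | Half-width, kg/m² | Power at 60 per arm |
|---|---|---|
| 0 | 0.524 | 80.2% |
| 0.02 | 0.519 | 81.0% |
| 0.05 | 0.511 | 82.2% |
| 0.10 | 0.498 | 84.2% |
| 0.20 | 0.469 | 88.1% |

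If the covariates explain nothing, power goes from 80.23% to 80.21%, a loss of about 0.02 percentage points.

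**3. Centre alone.** The table pools three covariates, so it does not give the effect of omitting centre. If centre explains a share R² and the arms are balanced within centre, the true SE is 0.265 × √(1 − R²). A model without centre still reports about 0.265. By the normal approximation:

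- one-sided error at the margin without centre = 1 − Φ(1.96 / √(1 − R²))
- power without centre = Φ((0.75/0.2647 − 1.96) / √(1 − R²))
- power with centre = Φ(0.75 / (0.2647 × √(1 − R²)) − 1.96)

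| Centre R² (assumed) | Error without centre | Power without | Power with |
|---|---|---|---|
| 0.05 | 2.2% | 81.5% | 82.8% |
| 0.10 | 1.9% | 82.1% | 84.8% |
| 0.20 | 1.4% | 83.5% | 88.6% |

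A simulation agrees. It used 120 completers, three centres in assumed shares of 40/30/30, half inpatients, and permuted blocks of 2 and 4. Both models adjusted for status.

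- **Centre R² 10%:** error about 1.6% without centre and 2.1% with it; power about 81% and 84%.
- **Centre R² 20%:** error about 1.6% and 2.6%; power about 83% and 89%.

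The Monte Carlo standard error is about 0.2 points for error, √(0.025 × 0.975/6000), and 0.7 points for power, √(0.8 × 0.2/3000). Omitting centre makes the test conservative and does not inflate the error rate.

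**The case against.** The strongest reply is that nothing here threatens validity. The primary test keeps its error rate, the sample size never relied on covariates, and the loss exists only if centre is prognostic. No section shows that it is. A reader might infer that the three centres run different care programmes. The article does not say so: Treatment as usual describes one multidisciplinary model, and the therapies are manualised and supervised. All of this stands. The variance shares above are assumptions, and the gain may be small.

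A reader might also infer that keeping age and illness duration out of the primary model is an error. It is not. They are not stratification factors, and a sparse primary model with a pre-specified richer sensitivity model is legitimate. It is only inefficient, given the importance that the protocol assigns to them.

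Nor are the Cochran-Armitage and Fisher tests wrong for secondary comparisons in a randomised trial. Replacing them with logistic or ordinal regression would change the target from a marginal comparison to a conditional odds ratio. Six strata (3 centres × 2 statuses) would average 120/6 = 20 completers each.

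The reply does not explain why one stratification factor enters every ANCOVA and the other enters none.

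**Conclusion.** The point holds as one of efficiency and of matching the analysis to the design. Centre stratifies the randomisation and enters no model, and the cost and categorical tests are stated without strata. Any resulting error is in the conservative direction. Two stronger conclusions a reader might draw are unsupported: that the non-inferiority test is invalid, and that the trial is undersized.

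The size cannot be read from the documents. For centre alone, an assumed share of 5 to 20% means a power loss of roughly 1 to 5 points from leaving it out. For centre, age and illness duration together, the range is 80.2% to between 81.0% (2%) and 88.1% (20%). Nothing in the article supports the upper end in particular. The figures also assume 60 completers per arm, a true difference of zero, and a residual SD of 1.45 before the added covariates.

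The case for changing rests on the asymmetry: the possible gain is modest to useful, and the loss if the covariates are uninformative is negligible.

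**What to change.** 1. Add centre as a fixed covariate to the primary ANCOVA, in both the ITT and PP analyses, and to the secondary ANCOVAs.
2. Preferably include age and illness duration in the primary model as well, with the model without them as the sensitivity analysis.
3. Run the Fisher-Pitman cost test with permutation within the randomisation strata. This keeps the named test. Hospitalisation is part of the cost and inpatients enter the trial partway through a stay, so status is a plausible source of cost variation, though the documents give no figure for it.
4. Stratified versions of the GOAS and amenorrhoea tests are optional.

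No new data are needed: centre and status are known from randomisation, and age and illness history are collected at baseline. The statistical cost is 2 degrees of freedom for centre (3 if the fourth site mentioned in the Discussion opens) and 2 for age and illness duration. The procedural cost is a change to the published primary covariate set while recruitment is under way, so it should be documented as an amendment with its reason before unblinding.

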## Hypotheses

We hypothesize that MFT is at least as efficacious as SFT in terms of weight and clinical evolution, and will be better accepted and not as costly in our treatment program.

We also hypothesize that some patient profiles will have better indications for one or another form of therapy.

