The Eating Disorders Symptom Impact Scale (EDSIS, [77]) is a 24-item self-report scale developed to assess the impact of eating disorder symptoms and behavior of an ill relative on the other family members. Four dimensions can be evaluated: Nutrition, Guilt, Dysregulated Behavior, and Social Isolation. Each item is rated on a 5-point Likert-type scale from 0 (“never”) to 5 (“nearly always”). Higher scores indicate higher impact of the symptoms on the family.

The Experience of Caregiving Inventory (ECI, [78, 79]) is a 66-item self-report questionnaire evaluating 10 dimensions of the experience of caring for an individual with a severe mental illness. The scale is composed of eight negative subscales*,* i.e., Difficult Behaviors, Negative Symptoms, Stigma, Problems with Services, Effects on the Family, Loss, Dependency, and Need for Backup, and two positive subscales, i.e., Positive Personal Outcomes and Good Aspects of the Relationship with the Patient. An overall score can also be produced. All items are rated on a Likert scale from 0 (“never”) to 4 (“nearly always”). Higher scores indicate greater difficulties in the experience of caregiving.

The Mental Illness Version of the Texas Inventory of Grief (MIV-TIG, [80]) was developed based on the Texas Inventory of Grief [81] for assessing grief in family members of a mentally ill individual. This self-report questionnaire comprises 24 items, 8 on past behaviors and 16 on current feelings, rated on a 5-point Likert scale from 1 (“completely false”) to 5 (“completely true”). A higher score indicates a higher level of grief.

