#### Secondary outcomes

Secondary outcomes are as follows:Change from baseline to months 12 and 18 in the overall patient’s clinical outcome (weight outcome, i.e., BMI > 10th percentile, presence of menstruation, GOAS category),Change from baseline to months 12 and 18 in the nature and seriousness of patient’s eating disorder symptoms (EDI-2 and EDDS scores),Change from baseline to months 12 and 18 in the nature and seriousness of patient’s other psychopathological symptoms (HADS, BDI-13, LSAS-CA-SR, MOCI, BVAQ-B, RSES, OSI, and C-SSRS scores),Change from baseline to months 12 and 18 in the nature and seriousness of parents’ psychopathological symptoms (HADS, BDI-13, BVAQ-B, RSES, ECI, EDSIS, and MIV-TIG scores),Change from baseline to months 12 and 18 in the quality of family relationships (FAD, SCORE-15, patients’ LEE scale, and parents’ FQ scores),Change from baseline to months 12 and 18 in the perceived quality of life (EDQOL and SOFAS scores for patients, WHOQOL-Bref, LHS, and CarerQOL-7D scores for parents),Number and duration of hospitalizations after inclusion,Patients’ and parents’ satisfaction (CSQ-8 and ECI scores) regarding the intervention,Cost of treatment between inclusion, 12 months, and 18 months thereafter.

Other measures will be explored as potential moderators or mediators of treatment outcome.

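### The ECI, a caregiving-experience scale, is tested as satisfaction with therapy and also listed as a parent symptom score, under two models that are not reconciled

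*Protocol article*

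**What the plan says.** All places are in the protocol article.

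- **Statistical methods, test of satisfaction.** "financial cost and satisfaction will be analyzed for the superiority of the MFT treatment over the SFT treatment". The instruments and time point follow: "We will compare subject and parent satisfaction with the treatments (as evaluated by the CSQ-8 and ECI) at 12 months using an ANCOVA". The covariate is given as "with the status of treatment is a co-variable at inclusion (outpatient or inpatient) as a pre-specified co-variable". No baseline score is named.
- **Statistical methods, other assessment scores.** These are analysed "using an ANCOVA, with the value of each respective variable at admission", together with treatment status at inclusion.
- **Secondary outcomes.** The ECI appears twice. It is among the parents' psychopathological symptom scores, as change from baseline to months 12 and 18: "HADS, BDI-13, BVAQ-B, RSES, ECI, EDSIS, and MIV-TIG scores". It appears again beside the CSQ-8 as a measure of satisfaction with the intervention.
- **Quality of life and degree of impairment.** The ECI is described as "evaluating 10 dimensions of the experience of caring for an individual with a severe mental illness", with eight negative and two positive subscales. "Higher scores indicate greater difficulties in the experience of caregiving".
- **Satisfaction with treatment.** The CSQ-8 is the only instrument under this heading. Its opening statement was reworded so that respondents rate the family therapy and not the whole programme.
- **Instruments.** Only the Short-CIDI and the CSQ-8 are exempt from the general schedule of baseline, 12 and 18 months. The ECI therefore has a baseline and the CSQ-8 does not.

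**The concern.** Cost and satisfaction are the two secondary outcomes that the plan singles out for a superiority test. Satisfaction is also the named outcome closest to the hypothesis that MFT "will be better accepted and not as costly in our treatment program". A reader of the results will take a positive satisfaction finding as evidence on how families received the therapy.

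The ECI does not measure that. A parent's experience of caregiving can ease because the child is less ill, whatever the parent thinks of the therapy sessions. Of its ten subscales only Problems with Services is close to satisfaction, and no rewording towards the family therapy is described for it, as was done for the CSQ-8. As a caregiver scale it also cannot supply the patient's view, although the sentence covers both patients and parents.

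Two further points are left open. The ECI is scored so that higher is worse, and the satisfaction test does not say which direction favours MFT. Nor is there a rule for which instrument carries the conclusion if the CSQ-8 and the ECI disagree.

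**Working it through.** **1. The plan's own figure.** No sample size or power is given for satisfaction. The Sample size section gives 60 evaluable patients per group for BMI (margin 0.75, SD 1.45, one-sided 2.5%, power 80%) and 75 per group after 20% dropout. The normal approximation gives 2 × 1.45² × (1.960 + 0.842)² / 0.75² = 58.7, so 59. With the t distribution, power is 79.6% at 59 and 80.2% at 60, so 60. Then 60 / 0.8 = 75. The figure reproduces. It is used below only as the number likely to be available per arm.

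**2. The two treatments of the ECI side by side.**

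| | As satisfaction | As parent symptom score |
|---|---|---|
| Listed in Secondary outcomes | yes | yes |
| Time points | 12 months (Statistical methods) | change from baseline to 12 and 18 months |
| Model | ANCOVA | ANCOVA |
| Treatment status as covariate | yes | yes |
| Baseline ECI as covariate | not named | yes |
| Stated aim | superiority of MFT | none specific to the ECI |

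Both are ANCOVAs with the same stratum covariate. They differ in the baseline term and in the label on the result. At 12 months they would give two estimates and two p-values from the same data.

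**3. What the missing baseline costs.** Let r be the correlation between baseline and 12-month ECI, given treatment status. Adjusting for baseline multiplies the residual variance by 1 − r², so leaving it out inflates the variance by 1/(1 − r²). The documents give no r, ECI standard deviation or target difference. The following are assumptions: r from 0.3 to 0.8, one ECI score per family, 60 per arm, two-sided 5%, and an illustrative true difference of 0.4 SD.

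The difference detectable with 80% power without baseline is (1.960 + 0.842) × √(2/60) = 0.51 SD. With baseline it is 0.51 × √(1 − r²).

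| r | 1 − r² | variance inflation | detectable difference with baseline (SD) | power at 0.4 SD with baseline |
|---|---|---|---|---|
| 0.3 | 0.91 | 1.10 | 0.49 | 63% |
| 0.5 | 0.75 | 1.33 | 0.44 | 72% |
| 0.7 | 0.51 | 1.96 | 0.37 | 87% |
| 0.8 | 0.36 | 2.78 | 0.31 | 95% |

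Without baseline, power at 0.4 SD is 59% whatever the value of r.

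**4. Bias.** Allocation is randomised 1:1, so the expected baseline ECI is the same in both arms. Leaving it out widens the interval but does not shift the estimate.

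**The case against.** The strongest reply is that the satisfaction model is the only one possible for the CSQ-8, which has no baseline, and that the ECI was simply written into the same sentence. The Secondary objectives list parental relief directly after satisfaction, which may explain the pairing. The ECI does contain a services subscale and two positive subscales, so calling it purely a burden scale would be too narrow. The analysis plan, which is not shown, may name the subscale. This explains how the text may have arisen and keeps the matter secondary. It does not remove the conflict: the published text gives the whole ECI two roles, and it applies the model without baseline to a scale that has one.

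A reader might also infer several stronger things that the documents do not support:

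- *That the satisfaction result as a whole is unsound.* The CSQ-8 was reworded to rate the family therapy, so a CSQ-8 result is about satisfaction. Only the ECI part is mislabelled.
- *That the ECI could mask a CSQ-8 difference.* No composite of the two is defined.
- *That the two ECI analyses are opposite.* They differ by one covariate.
- *That satisfaction is one of only two outcomes tested for superiority.* BMI is also tested for superiority once non-inferiority is shown.
- *That families who disliked the therapy are absent from the comparison.* Leaving therapy is not leaving assessment. The Discussion plans retention calls and online evaluation for families unwilling to attend, and the 20% dropout is a planning figure for BMI.

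That patients do not complete the ECI is an inference from its content, since the schedule figure is not shown.

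**Conclusion.** The point holds as an inconsistency in the role and model of one parent scale. The ECI is named as a measure of satisfaction against the protocol's own description of it, and its 12-month data fall under two models that the text does not reconcile. The practical risk is that a difference in caregiving experience is reported as a difference in satisfaction with MFT.

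The numerical cost concerns precision only. The variance of the ECI comparison is 1.33 times larger at an assumed r of 0.5 and 1.96 times larger at 0.7, and it ranges from 1.10 to 2.78 over r from 0.3 to 0.8. The inconsistency should be corrected before analysis, but it is confined to secondary outcomes and has no bearing on the BMI non-inferiority conclusion.

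**What to change.** 1. In Secondary outcomes and Statistical methods, define the satisfaction superiority test by the CSQ-8 alone, for patients and for parents, at 12 months, with treatment status at inclusion as covariate.
2. Analyse the ECI once, as a parent outcome under the general rule for assessment scores, with baseline ECI and treatment status as covariates. Report it as experience of caregiving.
3. If the Problems with Services subscale was intended as a satisfaction measure, name that subscale, state which direction favours MFT, and adjust for its baseline.

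The cost is a wording change to the secondary outcome list and the analysis text, recorded before the data are analysed. No new data are needed, because both instruments and the ECI baseline are already in the schedule.

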#### Eating disorder symptomatology

The Morgan-Russell Global Assessment Outcome Schedule (GOAS, [48–50]) evaluates the clinical state over the past 6 months using five clinician-rated subscales assessing Nutrition, Menstruation, Mental state, Psychosexual functioning, and Socioeconomic state. For each item, scores range from 0 to 12. A score for each subscale and an average outcome score can be calculated. Higher scores indicate better functioning. A global outcome category can also be defined [48]. A good outcome is characterized by a weight greater than 10th percentile and the presence of menstruation. An intermediate outcome is characterized by a weight greater than 10th percentile but amenorrhea (absence of menstruation for at least the past 3 months). Finally, a poor outcome is characterized by a weight bellow the 10th percentile and/or the presence of bulimic symptoms.

The Eating Disorder Inventory 2 (EDI-2, [51]) is a 91-item self-report questionnaire used to assess the presence of eating disorders (AN restrictive or binge purging types, bulimia nervosa, EDNOS, binge eating disorder). Each item is rated on a Likert-type scale, from “always” to “never.” EDI-2 comprises 11 subscales: Drive for Thinness, Bulimia, Body Dissatisfaction, Ineffectiveness, Perfectionism, Interpersonal Distrust, Interoceptive Awareness, Maturity Fears, Ascetism, Impulse Regulation, and Social Insecurity. Higher scores indicate higher levels of symptoms.

The Eating Disorder Diagnostic Scale (EDDS, [52]) is a 22-item self-report questionnaire used to assess the presence of anorexia nervosa, bulimia nervosa, and binge eating disorder. The scale consists of a combination of Likert scores, yes/no scores, frequency scores, and open-ended questions. The EDDS consists of a diagnostic scale and a continuous eating disorder symptom composite scale.

The Body Image Psychological Inflexibility Scale (BIPIS, [53]) is a 16-item self-report questionnaire that evaluates psychological inflexibility as it relates to body image distress. Each item is rated on a Likert scale, ranging from 1 (“never true”) to 7 (“always true”). Higher scores indicate higher levels of psychological inflexibility in body image.

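### GOAS category, menstruation and weight status are defined as change from baseline but tested without the baseline value or inpatient/outpatient status

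*Protocol article*

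**What the plan says.** Under Secondary outcomes, the first item is "Change from baseline to months 12 and 18 in the overall patient’s clinical outcome". It covers weight status relative to the 10th BMI percentile, menstruation and GOAS category. The Instruments section has all instruments given at baseline and again at 12 and 18 months, except the short CIDI (baseline only) and the CSQ-8 (not at baseline). The GOAS is therefore available at all three times.

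Under Statistical methods, quantitative assessment scores go into an ANCOVA with their own admission value and inpatient/outpatient status as covariates. The next sentence says "GOAS scores (with the three following outcomes: good, intermediate, and poor) will be compared between SFT and MFT" by Cochran-Armitage, with Somers' D and its 95% confidence interval. Amenorrhea and other qualitative variables get Fisher's exact test. No covariate is named for either test.

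Under Eating disorder symptomatology, the GOAS is described as "using five clinician-rated subscales assessing Nutrition, Menstruation, Mental state, Psychosexual functioning, and Socioeconomic state", and "A score for each subscale and an average outcome score can be calculated". The category is built differently: "A good outcome is characterized by a weight greater than 10th percentile and the presence of menstruation"; an intermediate outcome has the same weight criterion with amenorrhea; and "a poor outcome is characterized by a weight bellow the 10th percentile and/or the presence of bulimic symptoms".

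Under Randomization, allocation is stratified by inpatient/outpatient status and by center.

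**The concern.** The outcome definition and the test do not match. A follow-up table of menstruation by arm treats a patient who menstruated at entry and still does exactly like one whose menses returned during treatment. The first has not changed and the second has. The same holds for GOAS category and weight status. Entry is broad (AN and EDNOS, inpatients and outpatients), so baseline status may well vary between patients.

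These endpoints are also treated differently from every quantitative score in the same paragraph, with no reason given. The secondary objective asks whether MFT is at least as efficacious on these outcomes. A less precise comparison makes an inconclusive result more likely, and that is easily read as support for MFT.

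A related point is coverage. The secondary objectives name global clinical state separately from weight status and menstruation, yet the category consists of those two plus bulimic symptoms. The mental state, psychosexual and socioeconomic domains do not enter it.

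**Working it through.** **1. The plan's own figure.** The article gives no power, effect size or category rates for the GOAS. Its only calculation is for BMI change (margin 0.75 kg/m², SD 1.45, one-sided 2.5%, power 80%):

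- n per arm = 2 × (1.960 + 0.842)² × (1.45/0.75)² = 2 × 7.85 × 3.738 = 58.7, so 59 by the normal approximation. The exact t calculation gives 60 (power 80.2%), as stated.
- 60/(1 − 0.20) = 75 per arm, as stated.

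This fixes about 60 evaluable patients per arm. It says nothing about power for the categorical outcomes.

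**2. Definition against test.**

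| Outcome | Defined as | Planned test | Baseline used | Treatment status used |
|---|---|---|---|---|
| Quantitative scores | change to 12 and 18 months | ANCOVA | yes | yes |
| GOAS category | change to 12 and 18 months | Cochran-Armitage | no | no |
| Menstruation | change to 12 and 18 months | Fisher's exact | no | no |
| Weight status | change to 12 and 18 months | Fisher's exact (as a qualitative variable) | no | no |

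**3. What leaving out the baseline does.** For a binary outcome, let F1 and F0 be the follow-up proportions in the two arms and B1 and B0 the baseline proportions. The between-arm difference in change is

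(F1 − B1) − (F0 − B0) = (F1 − F0) − (B1 − B0).

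Randomization makes B1 − B0 zero in expectation, so testing F1 against F0 is valid. In the realised sample B1 − B0 is generally not zero. The planned tests ignore it, and they also leave between-patient variation that baseline could explain in the error.

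**4. Can the loss be sized?** For a normally distributed score, adjusting for a baseline with correlation r multiplies the residual variance by 1 − r². Both values of r here are assumptions:

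- r = 0.3: factor 0.91. A comparison with 80% unadjusted power at 60 per arm (0.516 SD) rises to 83.6%.
- r = 0.5: factor 0.75. Power rises to 89.9%.
- Lower limit: if all patients share one category at entry, the baseline category carries no information and the gain from it is nil.

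These figures illustrate the principle for a continuous score. They do not carry over to a three-level category whose baseline distribution and correlation the article does not give.

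**5. Category against average score.** This is a separate matter, and it also rests on assumptions.

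- If the category were a cut of one normal score with 80% power uncut, the trend test would have 70.5% power for a 25/50/25 split (loss 80.0 − 70.5 = 9.5 points), 66.9% for 30/20/50 (13.1 points) and 58.2% for 70/15/15 (21.8 points).
- The category is not such a cut. In a simulation with five correlated domains and the average score at about 80% power, a category built from the weight and menstruation domains had 34 to 58% power when all domains shared the effect. It had about 5% when the effect lay only in the three unused domains, and 97% or more when it lay only in weight and menstruation.

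The size of the difference, and even its sign, therefore depends on quantities the article does not supply.

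**The case against.** The best defence is that the planned tests are legitimate. In a randomized trial the follow-up distributions can be compared without baseline, the type I error already allows for chance imbalance, and allocation is stratified by treatment status. If most patients were in the poor category at entry, adjustment would bring little. All of this stands. It limits the point to precision and to the mismatch with the stated outcome, but does not remove that mismatch.

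A reader might infer more, and the article does not support it:

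- **That the GOAS is analysed only as three categories.** Only the category is listed as an outcome, so this is a natural reading. But the general ANCOVA sentence on assessment scores neither names nor excludes the GOAS average and subscales, and the parenthesis in the GOAS sentence may simply fix the test for the category form.
- **That categorising costs about 9 to 13 points of power.** That range needs an effect size borrowed from the BMI margin and a category that is a cut of a single score. The category as defined is not one, and the comparison can go the other way.
- **That mental state and social functioning are lost.** HADS, BDI-13 and SOFAS, among others, are separate outcomes under the baseline-adjusted ANCOVA. Only the psychosexual domain has no obvious substitute.
- **That the average score should replace the category.** The article cites a source for the category definition. Replacing it would be a trade-off, not the correction of an error.

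**Conclusion.** The point holds as a refinement of the secondary analyses. Three outcomes defined as change from baseline are assigned tests that use neither the baseline value nor inpatient/outpatient status, while the sentence before applies both to every quantitative score. This follows from the text alone and needs no assumed number.

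The consequence is a result that does not express the stated change and is less precise than the collected data allow. It is not a biased result. The loss of precision cannot be quantified from the article: it could be nil with a uniform baseline category, or material if baseline status varies and predicts outcome. The non-inferiority conclusion on BMI is not affected.

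The narrow content of the category is a reason to add the average score in support, not to drop the category.

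**What to change.** In Statistical methods:

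- Analyse GOAS category at 12 and 18 months by proportional-odds regression on arm, with baseline category and inpatient/outpatient status as covariates.
- Analyse menstruation and weight status by logistic regression on arm, each with its own baseline value and inpatient/outpatient status.
- Name a fallback for sparse cells: a stratified exact or Cochran-Mantel-Haenszel test.
- Keep Somers' D with its confidence interval as a descriptive measure.
- State that the GOAS average score and the five subscales are reported under the existing ANCOVA rule, as supportive results for global clinical state.

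The cost is a few sentences. The covariates and GOAS scores are already collected, so there is no new assessment and no change in sample size. There are two small downsides. Adjusted odds ratios are slightly harder to read than a table of categories by arm, which can still be shown alongside. The models may also be unstable if nearly all patients share one baseline category, which is why the fallback should be stated in advance.
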